#### Creation of Five Levels of Naturalness for Emotional Speech

Once acoustic features tendencies across naturalness levels will be defined, audio files from emotional human voices recordings will be edited in order to reduce naturalness in those speech signals. Spectral content will be filtered, intensity level and total duration (speech rate) will be adjusted. Acoustic signals edition will be realized using Matlab. For instance, if less naturalness is characterized by higher levels of harmonics-to-noise ratio [human speech is a noisy and continuous signal (Zatorre and Baum, 2012)], then frequencies that are not harmonics will be filtered. The edition of the signal will be applied on previously recorded in Stage 1 audio files for adult male, female, and children voices. Anger, fear, sadness, disgust, happiness, and neutral acoustic signals will be similarly adjusted. Naturalness will be progressively reduced to generate five different levels: from level 1: the less natural to level 5: the more natural voice. Level 1 will correspond to a 95% removal of naturalness, levels 2–5 will correspond to a 76, 57, 38, and 19% diminution, respectively. In accordance with this example, if less naturalness is characterized by higher levels of harmonics-to-noise ratio, then 95% of frequencies that are not harmonics will randomly be filtered for level 1, 76, 57, 38, and 19% of non-harmonics frequencies will be filtered for levels 2–5, respectively. All features defined as being part of naturalness characterization will be edited simultaneously.

Statistical analyses will be used to ensure that levels 1–5 and human voice differ as regard the acoustic parameters edited. Values obtained for each voice and emotion (e.g., adult male/anger, adult female/happiness, etc.) will be analyzed separately with one-way ANOVAs. Normality and homogeneity will be assessed using Shapiro–Wilk and Bartlett tests, respectively. In case of non-parametric distribution of the data, Kruskal–Wallis test will be applied. *Post hoc* comparisons will be conducted to assess specific differences (Tukey after ANOVA, Wilcoxon tests with *p*-value adjustment by Holm method after Kruskal–Wallis). In case of no statistical difference between levels, percentages of diminution of naturalness will be adjusted. Levels must differ for all parameters implicated in naturalness characterization.

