
#### Outcome Measures

##### ASRS questionnaire

The ASRS questionnaire is a standardized, reliable and validated set of questions targeted to parents or teachers of autistic people aged between 2 and 18 years to measure their autistic symptomatology (Simek and Wahlberg, 2011). It presents several advantages for its use in research (Goldstein, 2012). First, a wide range of autistic social and emotional behaviors are assessed, so that it makes the evaluation of generalization of learning to other social domains possible. Second, the scores provided are based on a normative TD sample, thus it considers the autism spectrum as a continuum with the general population making possible the comparison with a TD control group. The full-length version for 6–18 years old children and youths is composed of 71 items divided in three scales: ASRS scale, DSM-IV, and Treatment Scale. A 4-level scale is presented to the rater in order him to specify how often a particular behavior is used to be observed in the child or youth that is evaluated. Higher scores indicate higher symptoms severity according to the rater. In this study, a particular focus will be dedicated to Social/Communication, DSM-IV-TR, Peer and Adult Socialization and Social/Emotional Reciprocity domains. Parents of both groups will answer this questionnaire on pre-intervention (1st session) and follow-up sessions (2 and 6 weeks after the end of the intervention).

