##### Behavioral assessments

At pre- (1st session), mid- (7th session), end- (13rd session), and follow-up sessions (2 and 6 weeks after the end of the intervention), participants will be asked to answer the following behavioral task. It will consist of one block of stimulus pairs containing 244 pairs that will be presented at 60 dB via the Shure SRH1840 audio headset. The stimulus pair will be composed of either identical stimuli (50%; two neutral stimuli), or different stimuli [one neutral and one of the emotional deviants (50%; anger (10%), disgust (10%), fear (10%), happiness (10%), or sadness (10%)]. Fifty percent of pairs that contain a deviant stimulus will be composed of 1 neutral followed by 1 emotional stimulus, and 50% will be composed of 1 emotional followed by 1 neutral stimulus. Word pairs will be equally uttered with a male, woman, or child voice. The within-pair stimulus onset asynchrony will be 1,300 ms, and the between-pair stimulus onset asynchrony will be 2,600 ms. The order of stimulus pairs will be randomized between participants, but the stimulus sequence will be fixed. During this approximately 20-min task, participants will have to answer by pressing previously instructed keys on a laptop keyboard, if the emotional prosody of both stimuli of each pair will be the same or different. If they choose different, they will have to mention the emotion conveyed by the deviant (anger, disgust, fear, happiness, or sadness). Reaction times and correct/incorrect answers will be recorded. To make sure that the participant understands the task, three training trials will be presented before the test. Autistic participants will be accompanied by their parent if necessary.

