#### Data Analysis

##### Statistical analysis on ASRS scores

Group comparisons will be conducted by one-way ANOVAs on T-scores for each assessment session and symptom domain (Social/Communication, DSM-IV-TR, Peer and Adult Socialization, and Social/Emotional Reciprocity) separately.

Time comparisons (between assessment sessions) will be tested by one-way ANOVAs on T-scores for each group and symptom domain (Social/Communication, DSM-IV-TR, Peer and Adult Socialization and Social/Emotional Reciprocity) separately.

Normality and homogeneity of variances will be assessed by Shapiro-Wilk and Bartlett tests, respectively. In case of non-parametric distribution of the data, Kruskal-Wallis test will be applied. Post-hoc comparisons will be conducted to assess specific differences (Tukey procedure in case of ANOVA, Wilcoxon tests with *p*-value adjustment by Holm method in case of Kruskal–Wallis test).

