##### Statistical analysis on behavioral data

Group comparisons of reaction times will be conducted by a Group × Stimulus (neutral, anger, disgust, fear, happiness, or sadness) repeated measures ANOVAs on each assessment session separately. Time comparisons will be conducted by Assessment Session × Stimulus on each group separately. Normality of reaction times will be assessed by Shapiro–Wilk test. In case of non-parametric distribution of the data, a transformation will be applied. Mauchly’s test of sphericity will be used to evaluate homogeneity of variances and co-variances. In case of violation of sphericity, a Greenhouse-Geisser correction will be applied in order to test main effects significance. Post-hoc comparisons will be conducted to assess specific differences (Tukey procedure).

Group comparisons of number of correct answers will be conducted by one-way ANOVAs for each deviant and assessment session separately. Time comparisons (between assessment sessions) will be tested by one-way ANOVAs on number of correct answers for each deviant and each group separately. Normality and homogeneity of variances will be assessed by Shapiro–Wilk and Bartlett tests, respectively. In case of non-parametric distribution of the data, Kruskal–Wallis test will be applied. *Post hoc* comparisons will be conducted to assess specific differences (Tukey after ANOVA, Wilcoxon tests with *p*-value adjustment by Holm method after Kruskal–Wallis).

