Group 1 will be the experimental group and groups 2–4 will be controls. Children from group 2 will receive the same intervention as children from group 1, with the exception of the use of human voices only. This group will help to evaluate the efficacy of the use of synthesized voices in the intervention. Autistic participants will be randomly assigned to any of groups 1, 2 or 3. All four groups will be included in pre-, mid-, end and follow-up assessments.

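### Session-to-session comparisons of ASRS scores and correct answers treat repeated scores from the same children as independent samples, which makes the tests too conservative

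*Protocol article*

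**What the plan says.** Under *Statistical analysis on ASRS scores*: "Time comparisons (between assessment sessions) will be tested by one-way ANOVAs on T-scores for each group and symptom domain". The checks and fallback there are "Normality and homogeneity of variances will be assessed by Shapiro-Wilk and Bartlett tests, respectively" and "In case of non-parametric distribution of the data, Kruskal-Wallis test will be applied", followed by Tukey or Holm-adjusted Wilcoxon tests. Under *Statistical analysis on behavioral data*, accuracy gets the same treatment: "Time comparisons (between assessment sessions) will be tested by one-way ANOVAs on number of correct answers for each deviant and each group separately".

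The sessions are repeated on the same children. *Participants – Intervention* states "All four groups will be included in pre-, mid-, end and follow-up assessments". *ASRS questionnaire* gives three time points (pre, and 2 and 6 weeks after the intervention). *Behavioral assessments* gives five (pre, mid, end, and 2 and 6 weeks after).

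Other outcomes in the same stage are handled differently. Reaction times from the same task get Mauchly's test and a Greenhouse-Geisser correction, and the ERP time comparisons are named repeated measures ANOVAs.

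*Participants – Intervention* states a power of 0.90 for session comparisons, with 18 per group for ASRS and 15 per group for correct answers.

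**The concern.** A one-way ANOVA across sessions assumes that each session's scores come from different children. Here each child contributes three or five scores, and a child with severe symptoms at baseline is likely to score high later too. That stable variation between children should be removed from the error term. The one-way test keeps it there, so the standard error of a change between sessions is too large.

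The Discussion expects the intervention to reduce symptomatology and raise the number of correct answers at end and follow-up. With 18 children per group and withdrawals anticipated there, a test far stricter than its stated level could report no change over time where there was one.

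**Working it through.** **Inputs from the protocol.** n = 18 (ASRS) and 15 (correct answers) for session comparisons; 18 per group recruited; d = 0.8; alpha 0.05; m = 3 ASRS sessions and 5 behavioural sessions. **Assumption.** Within-child correlation ρ = 0.5. The protocol states this value, but not clearly for these two outcomes, so 0.3 to 0.8 is also shown.

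**Formulas.** f = d/2 = 0.4.
- One-way, k sessions: noncentrality λ = f²·k·n, df (k−1, k(n−1)).
- Repeated measures, m sessions: λ = f²·n·m/(1−ρ), df (m−1, (n−1)(m−1)).

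**Convention checked on other figures in the protocol.** Six emotions × 19 words, one-way: 0.916 (stated 0.92). ERP sessions, m = 5, n = 11, ρ = 0.5, repeated measures: 0.905 (stated 0.91). The convention reproduces these.

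**The two figures at issue do not reproduce.**
- ASRS, 3 sessions, n = 18. One-way: λ = 0.16 × 54 = 8.64, df (2, 51), power 0.726. Repeated measures: λ = 8.64/0.5 = 17.28, df (2, 34), power 0.954. Stated: 0.90.
- Correct answers, 5 sessions, n = 15. One-way: λ = 0.16 × 75 = 12.0, df (4, 70), power 0.771. Repeated measures: λ = 24.0, df (4, 56), power 0.978. Stated: 0.90.

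For 0.90 with three sessions at f = 0.4, the nominal one-way calculation needs 28 children per group; repeated measures at ρ = 0.5 needs 15.

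**Why the test is conservative.** With common variance σ² and correlation ρ, the null expectation of the between-session mean square is σ²(1−ρ), while the one-way error mean square has expectation σ². The F ratio is therefore shrunk by about (1−ρ). The standard error of a difference between two sessions is overstated by 1/√(1−ρ): 1.20 at ρ = 0.3, 1.41 at 0.5, 1.83 at 0.7 and 2.24 at 0.8.

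**Size by simulation** (20,000 trials per cell, equal correlations, linear session pattern scaled to f, n = 18, ρ = 0.5):

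| Sessions | f | One-way | Repeated measures |
|---|---|---|---|
| 3 | 0 (type I error) | 0.004 | 0.05 |
| 5 | 0 (type I error) | 0.002–0.003 | 0.05 |
| 3 | 0.4 (planned) | 0.75 | 0.95 |
| 5 | 0.4 (planned) | 0.87 | 0.99 |
| 3 | 0.25 (assumed) | 0.24 | 0.60 |
| 5 | 0.25 (assumed) | 0.27 | 0.74 |

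**Sensitivity to ρ.** At ρ = 0.3 and f = 0.4, power is about 0.74 against 0.86 (3 sessions) and 0.86 against 0.96 (5 sessions). At ρ = 0.8 and f = 0.25 with 3 sessions, it is 0.15 against 0.95.

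**Stage 2, secondary.** *Creation of Five Levels of Naturalness* derives levels 1–5 by editing the Stage 1 recordings, then says "Values obtained for each voice and emotion (e.g., adult male/anger, adult female/happiness, etc.) will be analyzed separately with one-way ANOVAs". The stated 17 words and power of 0.92 match an independent one-way calculation (f = 0.9/2 = 0.45, 5 levels: 0.916), so the pairing by recording is ignored there too. No size of effect was computed for that comparison.

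**The case against.** **One-way might mean one-way repeated measures.** This is hard to sustain. Bartlett and Kruskal–Wallis are independent-samples procedures, and the protocol names repeated measures or checks sphericity where it intends them.

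**Most of the power is lost.** A reader might infer this, but it fails at the protocol's own d = 0.8. There the loss is about 20 points with three sessions and 12 with five. Power falls by more than half only at f = 0.25, which is not in the document.

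**The protocol contradicts itself on the correlation.** The 0.5 appears in the sentence that leads into the ERP and reaction-time sizes. For correct answers the inputs are restated without it. The document shows different methods for similar data, not two conflicting statements.

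**The post hoc Wilcoxon tests are unpaired.** The protocol does not say whether they are rank-sum or signed-rank. The omnibus test before them is unpaired either way.

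**The efficacy comparison is compromised.** It is not. The randomised groups are compared at each session by tests between different children, where independence is correct. With positive within-child correlation the error is conservative, so it cannot create a false claim of benefit.

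**Stage 2 is only a stimulus check.** This stands. Ignoring the pairing makes the check stricter, and a non-significant result leads only to adjusting the editing percentages.

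**Conclusion.** The point holds for within-group change over time in ASRS T-scores and number of correct answers. For both, the protocol names a test that does not fit the data. The consequence is lost sensitivity: a true type I error well under 1% at ρ = 0.5, and a moderate power loss at the planned effect that becomes large if the true effect is smaller. Separately, the stated 0.90 for session comparisons is not what the named test delivers, even taken at face value with independent observations.

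These sizes rest on equal correlations between sessions, a linear session pattern and ρ = 0.5. The direction needs only positive within-child correlation. ERP time comparisons are unaffected, and reaction times apparently so, given their sphericity checks.

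**What to change.** - For time comparisons of ASRS T-scores and number of correct answers, replace one-way ANOVA with repeated-measures ANOVA and a Greenhouse-Geisser correction, as is already done for reaction times. A mixed model with a child random effect is an alternative.
- Replace Kruskal–Wallis in these comparisons with Friedman, and state that the Holm-adjusted Wilcoxon tests are paired signed-rank tests.
- Keep the one-way tests for group comparisons within a session.
- Restate the session-comparison power for three ASRS sessions and five behavioural sessions, with the correlation given for each outcome. At ρ = 0.5 and f = 0.4, the 18 children per group already planned give 0.954 and 0.993.
- Secondary: in the Stage 2 comparison of naturalness levels, treat the recording (word) as the repeated unit.

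The cost is analysis and sample-size text. Recruitment, visits and data collection do not change.

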##### Statistical analysis on behavioral data

Group comparisons of reaction times will be conducted by a Group × Stimulus (neutral, anger, disgust, fear, happiness, or sadness) repeated measures ANOVAs on each assessment session separately. Time comparisons will be conducted by Assessment Session × Stimulus on each group separately. Normality of reaction times will be assessed by Shapiro–Wilk test. In case of non-parametric distribution of the data, a transformation will be applied. Mauchly’s test of sphericity will be used to evaluate homogeneity of variances and co-variances. In case of violation of sphericity, a Greenhouse-Geisser correction will be applied in order to test main effects significance. Post-hoc comparisons will be conducted to assess specific differences (Tukey procedure).

Group comparisons of number of correct answers will be conducted by one-way ANOVAs for each deviant and assessment session separately. Time comparisons (between assessment sessions) will be tested by one-way ANOVAs on number of correct answers for each deviant and each group separately. Normality and homogeneity of variances will be assessed by Shapiro–Wilk and Bartlett tests, respectively. In case of non-parametric distribution of the data, Kruskal–Wallis test will be applied. *Post hoc* comparisons will be conducted to assess specific differences (Tukey after ANOVA, Wilcoxon tests with *p*-value adjustment by Holm method after Kruskal–Wallis).

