This project of investigation might encounter some pitfalls and unexpected results. Non-professionalism of actors recruited for emotional recordings during Stage 1 may affect the reliability of required prosodies. Nevertheless, the number of volunteers will be increased in order to generate four times more utterances than necessary to enable the selection of best actor participants. Furthermore, emotion recognition accuracy will be validated by supervised learning algorithm to ensure the quality of emotion discrimination based on acoustic features. Stage 2 aims to explore emotional recognition impairments in autism triggered by naturalness of human voices. We expect to observe a diminution of the amplitude of ERPs in the autistic population as a reflect of decreased attentional, sensorial, and cognitive emotional processing (Lartseva et al., 2015; Lindström et al., 2016, 2018). The autistic condition may also be characterized by hemispheric lateralization anomalies due to lateralized compensatory brain activity (Subbaraju et al., 2018). Impairments are expected to fade with the decreasing naturalness of voice stimuli. However, in the opposite case, no effect of naturalness on neural emotional processing by autistic children would be an evidence that the modulated acoustic parameters would not participate to autistic impairments. In the latter situation, or in case of enhancement of autistic impairments triggered by naturalness modulations, the acoustic edition of the stimuli will be reconsidered. Finally, Stage 3 expects the implementation of less natural voices in a robot-based intervention with the aim of improving emotion detection by autistic children. The 2-week intervention may imply a high rate of withdrawals whereas the sample size needed is relatively high. However, upon completion, we expect the intervention to trigger a reduction of autistic impairments (reduction of symptomatology, higher EEG activity, higher behavioral accuracy for emotion discrimination: smaller reaction times, and higher correct answers at end- and follow-up assessments).

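### Reaction times are analysed for all six stimuli but correct answers only for the deviants, so false 'different' answers on identical pairs go untested and faster or more liberal responding can resemble improvement

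*Protocol article*

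**What the plan says.** The task is described under Behavioral assessments in Stage 3 of the protocol article. It has 244 pairs, half identical (two neutral stimuli) and half containing one emotional deviant, with 10% of pairs for each of five emotions. The child presses a key for same or different. "If they choose different, they will have to mention the emotion conveyed by the deviant". For the data collected, "Reaction times and correct/incorrect answers will be recorded".

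The analysis is under Statistical analysis on behavioral data. On speed: "Group comparisons of reaction times will be conducted by a Group × Stimulus (neutral, anger, disgust, fear, happiness, or sadness) repeated measures ANOVAs", for each assessment session separately. Within groups, "Time comparisons will be conducted by Assessment Session × Stimulus on each group separately". On accuracy: "Group comparisons of number of correct answers will be conducted by one-way ANOVAs for each deviant and assessment session separately". The comparison between sessions uses "one-way ANOVAs on number of correct answers for each deviant and each group separately".

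The Discussion says what would count as a good result: "higher behavioral accuracy for emotion discrimination: smaller reaction times, and higher correct answers at end- and follow-up assessments".

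**The concern.** Two features of the plan combine badly.

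- **Coverage differs between the measures.** Neutral pairs enter the reaction-time models, but the accuracy analyses are defined by deviant. Answering 'different' to an identical pair is the error that shows whether a child is discriminating or simply saying 'different' more often. No planned test looks at it.
- **Speed is filed under accuracy.** The Discussion places shorter reaction times under behavioural accuracy, which they do not measure. No rule says how a faster but less accurate result would be read.

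At stake is the reading of the intervention's behavioural effect. If response style changes in the treated groups, through quicker pressing or a lower bar for calling a pair different, the planned analyses could show shorter times and more correct deviants while the ability to tell prosodies apart is unchanged.

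**Working it through.** The plan gives no figure on this point. The check sets the planned analyses against the task design and then illustrates the gap.

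**Trials and what is tested on them**

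- Identical pairs: 0.50 × 244 = 122. Reaction time analysed: yes, as the neutral stimulus. Correct answers analysed: not named.
- Deviant pairs: 0.50 × 244 = 122, or 0.10 × 244 = 24.4 (about 24) per emotion. Reaction time analysed: yes. Correct answers analysed: yes, per emotion.

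The accuracy analysis therefore sees hits and never sees false alarms.

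**Illustration of a pure response-bias shift**

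The inputs are assumptions, not from the documents: an equal-variance signal-detection model, sensitivity d', an initially unbiased criterion, and a shift s toward answering 'different' with d' unchanged. 'Correct' is taken to mean the same/different key press.

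- Hit rate = Φ(d'/2 + s)
- False-alarm rate = Φ(−d'/2 + s)
- Overall accuracy = (hit rate + 1 − false-alarm rate)/2, because the two pair types are equally frequent

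With d' = 1.5 and s = 0:

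- hits Φ(0.75) = 0.773, or 94.4 of 122
- false alarms Φ(−0.75) = 0.227, or 27.6 of 122
- overall accuracy 0.773

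With d' = 1.5 and s = 0.5:

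- hits Φ(1.25) = 0.894, or 109.1 of 122
- false alarms Φ(−0.25) = 0.401, or 49.0 of 122
- overall accuracy (0.894 + 0.599)/2 = 0.747

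Per emotion, the count that is tested rises from 18.9 to 21.8 of 24.4. The untested false alarms rise by about 21 pairs, and total correct answers fall from 188.7 to 182.2 of 244.

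**Range for the same shift of 0.5**

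| Assumed d' | Hits | False alarms | Overall accuracy |
|---|---|---|---|
| 1.0 | 69% → 84% | 31% → 50% | 69% → 67% |
| 1.5 | 77% → 89% | 23% → 40% | 77% → 75% |
| 2.0 | 84% → 93% | 16% → 31% | 84% → 81% |

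In every row the analysed count improves, while the unanalysed error and overall accuracy worsen. This model says nothing about speed; that reaction time also shortens is a further assumption.

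**Would restricting reaction times to correct trials be enough?**

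No, not for a criterion shift. Take a simple unbiased two-choice diffusion model (assumed drift 1, boundary ln 4, then 0.7 × ln 4). Accuracy is 1/(1 + e^(−av)) and falls from 0.800 to 0.725. Mean decision time is (a/2v)·tanh(av/2) and falls from 0.416 to 0.219, a ratio of 0.525. In this model correct and error responses have the same mean time, so correct-only times fall by about 47% as well.

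The restriction does help against careless fast guesses. A simulation with assumed inputs used 18 against 18 children, careful answers at 1.6 s and 80% correct, guesses at 0.8 s and 10% correct, and a between-child SD of 0.25 s. With 20% guesses in one group, the all-trial mean fell by 0.16 s and the correct-only mean by about 0.03 s.

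**The case against.** The strongest reply has four parts.

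1. **Trial selection is not stated.** A reader might infer that wrong answers are included in the reaction-time models. The article does not say so. It names the model factors and is silent on which trials enter, and a full plan may settle this. That silence is not an error in itself.
2. **Shorter times are not a stand-alone success criterion.** A reader might take the Discussion that way, but it pairs them with more correct answers: "smaller reaction times, and higher correct answers at end- and follow-up assessments". It also lists them beside symptom and EEG expectations.
3. **Accuracy is tested.** Correct answers are compared between groups and between sessions. Children who only guessed fast would look better on speed and worse on correct answers, not better overall. In the fast-guess simulation above, the loss of about 17 of 122 correct deviants was significant in essentially every run. That was a pooled test over all deviants, however, and the article plans one test per deviant.
4. **Hastier answering is not shown to be likely.** The Intervention section describes no time pressure and reinforces correct answers. All four groups take all the assessments, so task repetition alone does not separate them.

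These points stand, and they limit the concern to what follows. They do not answer the coverage gap. The third protects only against changes that lower deviant counts. A shift toward 'different' raises those counts, and its cost falls on identical pairs, which no accuracy analysis covers.

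**Conclusion.** The concern holds in a limited form. As written, the behavioural analyses leave false 'different' answers on half of the trials untested, state no link between speed and correctness, and list shorter times under accuracy. A shift toward quicker or more liberal 'different' responding could satisfy the stated expectations without better discrimination.

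The size cannot be taken from the documents. In the illustration, an unchanged ability yields a rise of about 12 percentage points in the tested hit rate at d' = 1.5 (9 to 15 points over d' from 2.0 to 1.0), while overall accuracy falls by 2 to 3 points. This rests on the assumed model and criterion shift, and on 'correct' meaning the key press. If it means naming the emotion correctly, the inflation of deviant counts need not follow, but false alarms remain untested and the reading of faster, less accurate results remains open. The diffusion and fast-guess figures are illustrations only.

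The documents do not support saying that error trials are included, that speed alone defines success, or that careless children would look better overall. The change is worth making because the method can be improved at almost no cost.

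**What to change.** - In Statistical analysis on behavioral data, add accuracy on the identical neutral pairs to the correct-answer analyses, between groups and between sessions. Alternatively, analyse a sensitivity index that combines hits and false alarms. State whether 'correct' refers to the same/different key or to the named emotion.
- Run the reaction-time ANOVAs on correct trials. This guards against fast guesses but does not cure a criterion shift, so it must be joined with the next rule.
- State that a shorter reaction time counts as improvement only if accuracy, including false alarms on identical pairs, is not lower. Otherwise report it as a speed-accuracy or response-bias shift.
- Reword the Discussion to match, so that reaction time is read jointly with accuracy and not listed as a form of it.

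Cost: wording and a small extension of the analysis. Reaction time and correctness are already recorded, so no new data are needed. The downside is somewhat fewer reaction times per child.

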##### Intervention

Autistic and TD participants involved in this study will have to meet the same criteria than those described in Stage 2. However, participants from Stage 2 will not be included in Stage 3 in order to avoid any bias elicited by a former exposition to the synthetic voices under study.

Sample size estimation was calculated with G^∗^Power software version 3.1.9.7 (Faul et al., 2007) for Cohen’s d effect size index of 0.8, correlations among repeated measures of 0.5, and statistical significance set at *p* < 0.05. For ERP analysis, results indicated that 13 participants in each group would be enough to provide an estimated power of 0.92 for group comparisons, and 11 participants in each group would be enough to provide an estimated power of 0.91 for assessment sessions comparisons. For behavioral analysis on reaction times, results indicated that 13 participants in each group would be enough to provide an estimated power of 0.91 and seven participants in each group would be enough to provide an estimated power of 0.93 for assessment sessions comparisons. For behavioral analysis on number of correct/incorrect answers, results indicated that 18 participants in each group would be enough to provide an estimated power of 0.92 for group comparisons, and 15 participants in each group would be enough to provide an estimated power of 0.90 for assessment sessions comparisons (Cohen’s d effect size index of 0.8, statistical significance set at *p* < 0.05). For behavioral analysis on ASRS scores, results indicated that 16 participants in each group would be enough to provide an estimated power of 0.92 and 18 participants in each group would be enough to provide an estimated power of 0.90 for assessment sessions comparisons.

A total of 72 participants will take part to this Stage and will be divided in four groups:

•Group 1: autistic children receiving robot, synthesized and human voices intervention (18 participants).•Group 2: autistic children receiving robot and human voice intervention (18 participants).•Group 3: autistic children without receiving intervention (18 participants).•Group 4: TD children without receiving intervention (18 participants).

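### Stage 3 accuracy is tested only emotion by emotion, so no planned group test addresses the general accuracy gain that the protocol expects

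*Protocol article*

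**What the plan says.** The behavioural task (Outcome Measures, Behavioral assessments) is described as follows: "It will consist of one block of stimulus pairs containing 244 pairs". Half of the pairs are two neutral stimuli. The other half contain one emotional stimulus, with anger, disgust, fear, happiness and sadness each making up 10% of all pairs. The task is given before, midway through and at the end of the intervention, and 2 and 6 weeks afterwards.

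Under Statistical analysis on behavioral data, accuracy is handled this way: "Group comparisons of number of correct answers will be conducted by one-way ANOVAs for each deviant and assessment session separately". The stated fallback is Kruskal–Wallis. No accuracy test across emotions is described, and no adjustment across the five emotions.

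The paragraph before it treats the other outcome of the same task differently: "Group comparisons of reaction times will be conducted by a Group × Stimulus (neutral, anger, disgust, fear, happiness, or sadness) repeated measures ANOVAs". The ERP analysis of deviant stimuli also keeps Deviant as a factor.

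On sample size for accuracy (Stage 3, Participants, Intervention): "results indicated that 18 participants in each group would be enough to provide an estimated power of 0.92 for group comparisons", with d = 0.8 and p < 0.05. The Discussion expects higher accuracy and more correct answers at the end and follow-up assessments, and does not single out any emotion.

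**The concern.** The expectation is general but the tests are specific. A reader who asks whether the intervention improves recognition of emotional prosody has to assemble the answer from five p-values per session, each based on a fifth of the emotional pairs and each at 0.05.

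Two things are at stake. First, each test has less power than one group comparison using all five emotions, unless scores are very highly correlated between emotions. Second, a benefit of the same size in every emotion will often be significant for some emotions and not others, and may then be reported as emotion-specific. Accuracy is the most direct measure of the trained skill, and no reason is given for treating it differently from reaction time.

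**Working it through.** **Inputs.** From the article: four groups of 18 (N = 72), d = 0.8, alpha 0.05, 244 pairs, five emotions at 10% each, five assessments. Assumed: f = d/2 = 0.40; the same effect in all five emotions; equal correlation ρ between emotion scores. The f = d/2 conversion reproduces another figure in the article: 19 words in each of six emotions gives 0.916, stated as 0.92. The article gives 0.5 for repeated measures at the head of the Stage 3 calculation but does not repeat it in the accuracy sentence, so a range is shown.

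**1. The plan's own figure.** One-way ANOVA, four groups: λ = N·f² = 72 × 0.16 = 11.52 on 3 and 68 df. Power is 0.80, not the stated 0.92; reaching 0.92 would take about 25 per group. This is a separate discrepancy. The comparison below starts from 0.80.

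**2. What each test uses.** 244 × 0.10 = 24.4 pairs per emotion; 5 × 24.4 = 122 emotional pairs; 24.4/122 = 1/5. Tests: 5 emotions × 5 sessions = 25.

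**3. Group effect over five emotions.** The mean of m = 5 scores has variance (1 + 4ρ)/5 relative to one score, so λ = N·f²·5/(1 + 4ρ). At ρ = 0.5, λ = 11.52 × 5/3 = 19.2 and power is 0.96. With the three randomised groups only (N = 54), power goes from 0.73 to 0.92.

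**4. One pairwise contrast, 18 v 18** (for example Group 1 v Group 2, which isolates the synthesized voice). Two-sided t test, noncentrality d·√(18/2) = 0.8 × 3 = 2.4: power 0.65. Pooled at ρ = 0.5, d becomes 0.8/√0.6 = 1.03 and power is 0.85.

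| ρ | Four-group: one emotion → five | Gain (points) | Pairwise: one emotion → five | Gain (points) |
|---|---|---|---|---|
| 0.3 | 0.80 → 0.99 | 19 | 0.65 → 0.94 | 30 |
| 0.5 | 0.80 → 0.96 | 16 | 0.65 → 0.85 | 21 |
| 0.7 | 0.80 → 0.90 | 10 | 0.65 → 0.76 | 12 |
| 0.8 | 0.80 → 0.87 | 7 | 0.65 → 0.72 | 8 |
| 0.9 | 0.80 → 0.83 | 4 | 0.65 → 0.68 | 4 |

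**5. The five tests read together.** Simulated with normal scores, four groups, f = 0.40 in every emotion and ρ = 0.5:

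- All five tests significant: about 50% of trials. One to four significant: about 48%.
- At least one significant at 0.05: about 98%. With no effect at all, the same rule gives about 19% false positives per session (for five independent tests, 1 − 0.95⁵ = 23%).
- At least one significant at 0.05/5 = 0.01: about 90%, against 96% for the single joint test, a gain of about 6 points.

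**The case against.** The strongest reply is that the other emotional pairs are not lost. A reader might infer that four fifths of the emotional data go unused, but the document does not support that: those pairs are analysed in the sibling tests. If the question is whether there is any effect on accuracy, the fair comparator is a corrected any-of-five rule, and the gain is then about 6 points. This stands. The article describes no such correction, however, and the uncorrected rule has about 19% false positives per session.

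A reader might also take 16 to 21 points as the range of the loss. It is not a range: 16 is the four-group test and 21 a pairwise contrast, both at a correlation of 0.5 that the accuracy sizing does not state. Taking the stated 0.92 at face value would leave a gain of only about 7 points at 0.5, but 0.92 does not follow from the stated inputs.

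Nor does the plan's sizing demonstrate the cost, though 13 per group for reaction times against 18 for accuracy invites that reading. Neither stated power reproduces under the formulas used here: 0.87 against 0.91 for reaction times with six stimuli, and 0.80 against 0.92 for accuracy. The article also does not say which effect was sized for reaction times.

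There are good reasons to want emotion-specific results: the child names the emotion, and there is a specific story for each. That supports reporting them, not having them alone. Two further limits stand. Pooling dilutes an effect confined to one or two emotions. And a five-emotion model, like the current plan for accuracy, leaves out the identical neutral pairs, so it does not deal with a child's general tendency to answer that stimuli differ.

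**Conclusion.** The point holds as one of efficiency and interpretability. The plan fixes accuracy as separate per-emotion tests, and none of its group tests matches the general gain it expects. If the effect is d = 0.8 and similar in all five emotions, with 18 per group, the four-group power is 0.80 per emotion and 0.96 for the joint group effect at a between-emotion correlation of 0.5. The gain shrinks to about 4 points at 0.9, and is about 6 points at 0.5 against a Bonferroni-corrected any-of-five rule.

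The risk of misreading does not depend on choosing a comparator: at a correlation of 0.5, a uniform benefit gives a mixed pattern in about 48% of trials. These figures treat scores as normal; bounded counts could shift them. The per-emotion tests are not invalid in themselves. They do not answer the overall question.

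**What to change.** For each assessment session, replace the per-deviant one-way ANOVAs on number of correct answers with one Group × Deviant model, with child as the repeated unit. A mixed logistic model on trial-level correct/incorrect answers is preferable, because the counts are bounded and the Kruskal–Wallis fallback does not carry over to a two-factor design. State that the Group effect over the five emotions is the overall accuracy result. Report per-emotion differences through the Group × Deviant interaction and its post hoc contrasts.

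This changes analysis wording only and needs no extra children, sessions or data. The price is that emotion-specific claims become secondary, and an effect limited to one or two emotions would be weaker in the overall test, though still visible through the interaction and contrasts.
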